##### Safety analysis

For the safety co-primary objective, AEs will be analyzed in total and by body system. Tables will show the number of AEs observed and the number and percentage of participants experiencing them within a system organ class or within preferred term category by severity or by relationship to the study product. Participants with multiple AEs within a category will be counted once under the maximum severity or the strongest recorded causal relationship to the study product. Differences between AE rates in the intervention groups will be assessed by means of generalized estimating equations to account for the cluster design.

A listing of SAEs reported to the DSMB will provide details of the events including severity, relationship to the study product, time between onset and last treatment, and the number of treatments administered and received by the study participant.

The number and percentage of study participants who discontinue treatment and who terminate from the study early will be tabulated by reason and treatment arm.

### Interim analyses {21b}

There will be three rounds of MDA separated by a month each. Safety data will be collected in the month following each administration. Given the delay in reporting and the ample experience with ivermectin in MDA, there will be no interim analyses

### Methods for additional analyses (e.g., subgroup analyses) {20b}

These are detailed in the SAP.

### Methods in analysis to handle protocol non-adherence and any statistical methods to handle missing data {20c}

Missing data frequency and patterns will be studied for the main variables and, if appropriate, multiple imputation techniques will be considered. Unused and spurious data will be excluded from data analysis as soon as it is recognized

Any deviations from the statistical methods explained in the protocol will be described and justified in the final report.

The SAP will be reviewed by the DSMB and updated where necessary as a result of interim analyses of the data. A formal record will be kept detailing when the SAP was finalized. It will suffice to update the statistical analysis plan with the considerations suggested from the reviews as well as any protocol amendment.

A detailed review of the SAP will also be carried out prior to the study close-out to ensure any protocol amendments have been incorporated. Statistical changes such as rationale for newer or improved analytic methods for the data will be documented

### Plans to give access to the full protocol, participant level-data and statistical code {31c}

Per the contractual agreement, the database will be made publicly available upon completion of the project

## Oversight and monitoring

### Composition of the coordinating center and trial steering committee {5d}

ISGlobal is the coordinating center. The PI, CSO, project manager, GCP-QA focal person, and program officers work on a day-to-day basis for the management of the trials. There are also regular weekly meetings with other personnel including the financial officer and communications.

There is a Trial Steering Committee that meets twice a year and is composed of field experts and country representatives.

### Composition of the data monitoring committee, its role and reporting structure {21a}

An independent DSMB with seven members including representatives of each study country has been assembled for this study. The details for the operation and responsibilities of the DSMB are defined in a DSMB Charter. The Charter delineates the composition, duties, responsibilities, and procedures of the DSMB, the data required at each meeting as well as any analyses that will be conducted.

After each DSMB meeting, the Chairperson will issue a written report describing all recommendations

### Adverse event reporting and harms {22}

Participants will be asked to record signs and symptoms associated with known ADRs in the diary for review by the field worker during the post-dosing safety visit occurring 1 month post dose.

The participant will be asked to provide information on any other events, physician visits or hospitalizations, and treatment taken during day 0 through day 6 during the post dosing safety visit.

Participants will be asked about any AEs occurring after the 6th day and up to the next dosing day. As the IP will no longer be present in the participant’s system at detectable levels, these events will be deemed unrelated to the IP. These events will be recorded on adverse event logs, which form part of the source data and will not be included in the data analysis. These unrelated events will be reported to IRBs and DSMB in 6 monthly line listings unless local regulations specify otherwise.

Participants shall be encouraged to contact the Investigator by telephone to report severe events in case the investigator deems an ad hoc visit by the participant to the site or local clinic is required.

The investigator and/or sub-investigator with assistance from delegated study staff will visit local hospitals in the district to review in- and out-patient records to ensure all adverse events for trial participants are captured. The investigator or appropriately qualified sub-investigator shall determine the severity and causality for all events.

All AEs and SAEs occurring from the time a volunteer consents to participate in the study until 4 weeks after he or she has completed or discontinued the IP must be recorded in the Patient’s electronic records and trial database. BOHEMIA will use MedDRA coding and CIOMS forms to ensure standardization of terminology across the trial.

Importantly, SAEs will have to be reported, either by email or by Fax, by the site PI/Co-PI or sub-investigator to IntuVigilance Limited within 24 h of awareness of an SAE.

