#### Safety

Rate of AEs and serious adverse events (SAEs) and the difference between ivermectin and albendazole.

Secondary

Complementary efficacy analysis methodsT﻿ime to first positive RDT in children in the cohortMolecular force of infection in a subset of children in the cohortMalaria case incidence in all ages presenting at a health facilityMalaria prevalence in all ages one month after the last doseMultiplicity of infection in all ages one month after the last dose

2.Complementary safety variablesObserved tolerability of the doseRate of SUSARsAEs and SAEs by organ system

3.PharmacokineticsWhole blood concentrations of ivermectin in dried blood spots.

4.Impact of ivermectin against selected ectoparasites and NTDs in the dosage regimen chosenSerial prevalence of scabies using a simplified version of the algorithm described by Mahe et al. [53] which consists of two questions and an evaluation of exposed skin on hands, knees, elbows, armpits, wrists, and feet.Serial prevalence of head lice by visual inspection over three minutes in scalp sites of predilection for head lice: the back of the ears, temples, and neck [54].Serial prevalence of Tunga penetrans via visual inspection of the skin in both feet and applying the Fortaleza scale [55].Serial prevalence and severity of bed bug infestation by direct questions about bedbugs in the house, and visual inspection of exposed skin and sleeping rooms for evidence of bed bug bites or bed bug infestation.

5.Prevalence - incidence correlationMalaria infection incidence in children (under 5 years) in the pediatric active cohort at community and health facility levelsMalaria prevalence at all ages

6.Relationship between active and passive surveillanceInfection incidence in children at the community level (active surveillance)Infection incidence in children at the health facility level (passive surveillance)

7.Performance of RDTs vs PCRResults correlation between HRP2 and pLDH-based RDTsResults correlation between RDTs and PCRProportion of RDT-negative but PCR-positive infections

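### The adverse event section removes AEs after day 6 from the data analysis by rule, contradicting its own causality statement and the co-primary safety comparison

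*Protocol article*

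**What the plan says.** Objectives {7} makes safety co-primary. Outcomes {12} defines the endpoint as "Rate of AEs and serious adverse events (SAEs) and the difference between ivermectin and albendazole". The Safety analysis text under Statistical methods {20a} counts AEs overall, by body system, by severity and by relationship to product, and compares arms with generalized estimating equations. Neither place limits the time since dosing.

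Adverse event reporting and harms {22} does set a limit. The post-dosing visit covers events and "treatment taken during day 0 through day 6 during the post dosing safety visit". Then: "Participants will be asked about any AEs occurring after the 6th day and up to the next dosing day". On the ground that the product is no longer detectable, "these events will be deemed unrelated to the IP". They go on logs "which form part of the source data and will not be included in the data analysis", and reach the ethics boards and the DSMB as six-monthly line listings unless local rules differ.

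The same section also says that the investigator or a qualified sub-investigator "shall determine the severity and causality for all events", and that AEs and SAEs from consent "until 4 weeks after he or she has completed or discontinued the IP must be recorded" in the trial database. SAEs have a separate 24-hour reporting route. Interim analyses {21b} adds: "Safety data will be collected in the month following each administration".

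**The concern.** A randomised comparison of event rates does not need a causality judgement. Background illness is expected in every arm, and the difference between arms carries the drug effect. Removing events because they are presumed unrelated assumes the answer for that period. An AE type that starts after day 6 contributes nothing to the analysed difference, whatever its true frequency in either arm. The planned tables by relationship to product would also be partly filled in by the rule and not by assessment.

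The rule is also at odds with the rest of the plan. Two analysts working from the same document could produce different co-primary safety results, one following section {22} and the other following Outcomes {12} and the Safety analysis text.

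The rule on not re-challenging in section {11b} turns on drug-relatedness. If relatedness is fixed by calendar day in one sentence and by investigator judgement in another, that rule has no single basis. The passages must be reconciled.

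**Working it through.** The plan gives no figure for the safety window, so there is none to reproduce. The check has two parts.

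**Comparing the texts**

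- Causality: "these events will be deemed unrelated to the IP" against "shall determine the severity and causality for all events". Both govern the same events, so this is a direct contradiction.
- Analysis set: "which form part of the source data and will not be included in the data analysis" against an endpoint and a Safety analysis text that cover AEs with no day-6 limit. This is a conflict over which events are compared.
- Collection and recording: "Safety data will be collected in the month following each administration" and "until 4 weeks after he or she has completed or discontinued the IP must be recorded". These say what is gathered and stored. A narrower analysis does not strictly contradict them, but they show that the late events should already be available.

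**Size of the excluded window**

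Inputs from the Participant timeline {13}: doses on Days 1, 31 and 61, and the final safety visit on Day 91. Each interval is therefore 30 days, and the total is 90 days. Days retained per dose: 7 if dosing is day 0 (the count used in section {22}), or 6 if dosing is Day 1 (the count used in the timeline).

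Share excluded per interval = (interval − days retained) / interval.

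- 7 days kept: (30 − 7)/30 = 23/30 = 76.7%
- 6 days kept: (30 − 6)/30 = 24/30 = 80.0%

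Sensitivity to visit windows: Days 31 and 61 each carry ±3 days. The first interval can then run 27 to 33 days, and the second from 58 − 34 = 24 to 64 − 28 = 36 days. The extremes are (24 − 7)/24 = 70.8% and (36 − 6)/36 = 83.3%.

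The rule runs to the next dose, and the third dose has none. Over the 90 days:

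- Rule applied after all three doses: 3 × 23 = 69, 69/90 = 76.7%; or 3 × 24 = 72, 72/90 = 80.0%
- Rule applied after doses 1 and 2 only: 2 × 23 = 46, 46/90 = 51.1%; or 2 × 24 = 48, 48/90 = 53.3%

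These are shares of calendar time. No AE rates are given, so they cannot be turned into shares of events or into bias in the difference.

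**The case against.** A short post-dose window is a recognised tolerability choice, and it applies equally to all arms. Days 7 to 30 bring in background illness, and the protocol itself describes cyclones, floods and a cholera outbreak. That noise can dilute rate ratios. If ivermectin reduces malaria, malaria AEs may also be fewer in its arms, so an all-AE comparison could look more reassuring. This stands as a reason to report both windows. It does not justify deeming events unrelated by date or leaving the plan contradicting itself.

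Several stronger readings are tempting, and the documents do not support them:

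- A reader might infer that late SAEs are dropped. The rule speaks of AEs, while the same section names AEs and SAEs together when it means both. SAEs are reported within 24 hours, and those reported to the DSMB are listed with time since last treatment. Whether they enter the rate comparison is unclear, not settled. Nor does it follow that the DSMB sees late SAEs only every six months.
- A reader might infer that cumulative harm is invisible. Days 0 to 6 after doses 2 and 3 are analysed, so toxicity that builds with repeat dosing can show there.
- A reader might infer that the detectability claim is wrong because pharmacology sampling ends at the Day 3 visit. That schedule means the trial cannot confirm the claim, but it does not refute it.

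**Conclusion.** The concern holds as a stated rule that is wrong for a randomised safety comparison and inconsistent with the rest of the protocol. It is not a detail left to the analysis plan: the exclusion is written down, and it conflicts with the causality sentence in the same section and with the co-primary endpoint and its analysis.

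If followed, the rule removes about 77% to 80% of each 30-day interval, on nominal visit days. If dose 3 is outside the rule, it removes 51% to 53% of the 90 days. The plan does not say which reading of dose 3 applies. It would go too far to say that the co-primary comparison will certainly ignore that share, because Outcomes {12} and the Safety analysis text support the opposite reading. The size and direction of any effect on the ivermectin versus albendazole difference are unknown. Because a co-primary result depends on which text governs, this should be settled before unblinding.

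**What to change.** In section {22}, delete the automatic classification as unrelated and the exclusion from analysis, and have causality assessed individually for each event.

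Before unblinding, state one window for the co-primary comparison, consistent with Outcomes {12} and the Safety analysis text: all recorded AEs and SAEs from first dose to 4 weeks after last dose, by arm, regardless of attributed causality, with SAEs after day 6 explicitly included. This also settles the handling of the third round. Report days 0 to 6 after each dose alongside it as a pre-specified acute-tolerability analysis, and state whether dosing is day 0 or day 1. Reconcile the no-re-challenge rule in section {11b} with whichever text governs relatedness.

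The cost is protocol and analysis-plan wording, individual causality assessment of the late events, and entry of any that sit only on logs. No visits are added: participants are already asked about these events, and the protocol already requires them in the trial database. The statistical price is more background noise from the later days and a possible contribution from malaria AEs that differ by arm through efficacy. Showing both windows lets the reader see each effect. At submission the protocol described data collection as ongoing and the analysis team as blinded, so the change could still be made without knowledge of the results.

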### Frequency and plans for auditing trial conduct {23}

To ensure compliance with GCP, all applicable regulatory requirements, as well as the protocol, ISGlobal, Unitaid (the funder), RAs, and/or ethics committees may conduct a routine quality assurance audit or regulatory inspection of this study. Additionally, in instances where there is a high occurrence of non-compliances at a trial site or misconduct is suspected, any one of the parties may institute a for-cause audit/inspection.

Such audits/inspections can occur at any time during or after the completion of the study. If an audit or inspection occurs, the investigator and the research institution agree to allow the auditor/inspector direct access to all relevant documents and to allocate his/her time and the time of his/her staff to discuss findings and any relevant issues.

### Plans for communicating important protocol amendments to relevant parties (e.g., trial participants, ethical committees) {25}

These trials shall be conducted under the auspices of properly constituted Ethics Committees as defined by ICH-GCP E6 (R2) Guidelines. These committees shall review and approve all aspects of the study and subsequent amendments as stipulated by the ICH-GCP Guidelines prior to and during the conduct of the study.

### Dissemination plans {31a}

A publication policy and publication have been completed and signed off by all consortium members. Dissemination of study products in conferences or publications will be conducted following international guidelines. Findings from this study will not be disseminated without adequate leadership and representation of local researchers.

## Discussion

Implementing such a large trial under GCP-ICH standards in remote rural settings in Mozambique is challenging at several levels:ICH standards have been developed primarily for hospital-based work in high-income countries and they do not always take into consideration the environmental or cultural context of rural Africa. A clear example is the legal guardianship of minors. Can the primary caretaker (an “auntie”) provide consent for a child if both parents are absent or dead even if this primary caretaker does not have written proof of legal guardianship?There is a need to have community buy-in by involving local personnel in the field work, yet the scarcity of trained personnel increases the costs and length of trainingCluster randomization brings additional complexities as community engagement and early handling of rumours requires a fully dedicated teamMalaria is a seasonal disease, and implementing a mass drug administration program during the rainy season carries enormous logistical challenges including degraded roads, floodings, and general supply constringentThe Mozambican team faced five cyclones and severe floodings followed by a cholera outbreak. This means a surge in the number of deaths in study participants. This put a serious strain on the local team in order to keep the strict reporting timelines required by ICH. Appropriate resources were put in place including the procurement of satellite phones for usage in areas with no cell phone networkCollecting large amounts of data from the field with limited connectivity requires complex logistical operations such as physically transporting tablets to an area with 3G coverage for upload and refresh

## Trial status

Protocol version 4.2 dated 13 March 2022. Recruitment started on 15 March 2022 in Mozambique. Recruitment was completed in July 2022. Follow-up of the active pediatric cohort will continue until October 2022. Follow-up of the pregnancy cohort will continue until March 2023

We submit the protocol after finishing recruitment but before the completion of the follow-up of the last patient envisioned for March 2023. This is mentioned in the structured summary and is because of the following reasons:

Delayed ethical approval given discussions between the WHO ethics committee and that of Mozambique which were only solved the day before implementation.Implementation difficulties such as floodings, a cholera outbreak and rumors for the first 4 months required the full attention of the study team.The Tanzanian government issued a stop work order for the district of Rufiji given the potential this meant that the team had to seek an alternative site while implementing in Mozambique. This has been found in Kenya and the protocol is currently undergoing review there.

## Data Availability

Per the contractual agreement, the database will be made publicly available upon completion of the project

## Abbreviations

ADR: Adverse drug reaction
AE: Adverse event
AL: Artemether-lumefantrine
AUC: Area under the curve
CDC: Centers for Disease Control and Prevention
CIBS: Ethics Committee of CISM
CISM: Centro de Investigação em Saúde De Manhiça
CNS: Central nervous system
CRA: Clinical Research Associate
CRF: Case Report Form
DEC: Diethylcarbamazine
DOT: Directly observed treatment
DSMB: Data and Safety Monitoring Board
eCRF: Electronic Case Report Form
EDC: Electronic data capture
EMA: European Medicines Agency
EU: European Union
FDA: *Food and Drug Administration*
GCP: *Good Clinical Practice*
GSK: *GlaxoSmithKline*
HFW: Health facility workers
ICH: *International Conference on Harmonisation*
IHI: Ifakara Health Institute
IP: *Investigational Product*
IRB: *Institutional Review Board*
IRS: Indoor residual spraying
LF: Lymphatic filariasis
LFU: Lost to follow-up
LLIN: Long-lasting insecticidal nets
LMP: Last menstrual period
MDA: Mass drug administration
MoH: Ministry of Health
MUAC: Mid-upper arm circumference
NDA: New drug application
NMCP: National Malaria Control Programme
NTD: Neglected tropical disease
PCR: Polymerase chain reaction
PID: Participant identifiers
PI: Principal Investigator
PK: Pharmacokinetics
pLDH: Parasite lactate dehydrogenase
PMI: President’s *Malaria* Initiative
PPC: Preferred product characteristics
RA: Regulatory authority
RDT: Rapid diagnostic test
REC: Research Ethics Committee
SAE: Serious adverse event
SAP: Statistical analysis plan
SMC: Seasonal malaria chemoprevention
STHs: Soil-transmitted helminths
SUSAR: Suspected unexpected serious adverse reaction
VCAG: Vector Control Advisory Group
WHO: World Health Organization
